### Other data

Other data will include age, sex, surgery type, type and dose of anaesthetic, anti-anxiety medications, history of previous surgeries, and discharge data. This data will be collected from the participant’s health record by the researcher.

### Sample size {14}

Based on the previous study by Bekelis et al. [24], a sample of 150 participants (75 per group) will provide 80% power to detect a 20% change on the 100-point VAS-A between groups with a type 1 error rate of 5%. This calculation assumes a dropout rate of 15%.

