### Hypothesis {6b}

Compared with standard care, a VR intervention delivered during the preoperative period will significantly reduce perioperative anxiety in adult elective surgical patients by 20 points on a 100-point visual analogue scale for anxiety (VAS-A).

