### Statistical plan {20a}

Characteristics of groups will be summarised using counts and percentages for categorical variables and means and standard deviations for continuous variables. The primary outcome (anxiety at Time 2 and Time 3 in stacked format) will be compared between groups at each follow-up time point using a linear mixed-effects regression model, with fixed effects including treatment arm time (categorical), the interaction between treatment and time, anxiety time point (either Time 2 or Time 3), surgical type (stratification variable), and the baseline value of the outcome variable. Differences in mean VAS-A scores between groups at each time point will be presented together with 95% confidence intervals and *p*-values. Continuous secondary outcomes with repeated measurements will be compared using the same model. Hospital length of stay will be compared using the rank-sum test. Patient satisfaction will be compared using an independent sample *t*-test and descriptive statistics will be used to summarise the VRSQ.

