## Discussion

Preoperative anxiety is a common condition that adversely impacts approximately 320,000 Australians each year [38]. Unfortunately, preoperative anxiety is frequently overlooked and undertreated. This has become exacerbated with the move to day-of-admission surgery and limited preoperative preparation.

Anxiety should not be overlooked because it has severe effects on patients’ adverse psychological and physiological effects. The psychological effects include a feeling of unease, excessive fear, worry, tension, apprehension, catastrophising, or obsessive thinking [39, 40]. The physiological effects include increased respiratory rate, heart rate, and blood pressure [39, 40]. All of these effects can lead to an increase in the risk of postoperative complications such as pain, need for a greater dose of anaesthesia, delayed wound healing, infection, prolonged recovery, longer hospitalisation, and patient dissatisfaction [12, 41, 42].

There are significant costs associated with these related postoperative complications [43]. However, there is a potential cost saving from preventing or reducing anxiety. Non-pharmacological treatments, like VR, that can be administered by nurses or even self-administered by patients, offer a simple and cheap option for addressing the burden and impact of perioperative anxiety [17].

This current study has several strong features which include the design of a randomised controlled trial (RCT) in accordance with the CONSORT guidelines which is considered the ‘gold standard” in evidence-based research and will provide strong evidence of the effectiveness of using VR on perioperative anxiety compared with non-clinical trial design [44]. In addition, it will be the largest study in adults and the first to screen participants’ level of anxiety using a validated tool—APAIS—before the intervention [28, 29]. Screening for moderate to severe anxiety ensures that the study population requires treatment, which will reduce the dilution of the intervention’s effectiveness, giving a more accurate insight into its clinical relevance. Moreover, this is believed to be the first RCT to combine patient-reported anxiety with the measurement of saliva cortisol level as a biological marker of the stress response.

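### The stated 80% power for a 20-point VAS-A difference needs an SD of about 40, above what any single-peaked 0–100 score can have, so the 80% or the 20 points is probably misstated

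*Protocol article*

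**What the plan says.** Under Sample size {14}, the protocol article bases its calculation on an earlier published study. With 150 participants, 75 to each arm, it claims that this size "will provide 80% power to detect a 20% change on the 100-point VAS-A between groups with a type 1 error rate of 5" per cent. On losses it adds: "This calculation assumes a dropout rate of 15" per cent. No SD, test or sidedness is given.

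Hypothesis {6b} expresses the effect in absolute terms: VR will significantly reduce anxiety "by 20 points on a 100-point visual analogue scale for anxiety (VAS-A").

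Under Statistical plan {20a}, VAS-A at T2 and T3 is analysed in a linear mixed model that includes the baseline value as a fixed effect. Group differences at each time point are "presented together with 95% confidence intervals" and p-values.

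**The concern.** Sample size, dropout, alpha and power together fix the detectable difference in SD units. Once the hypothesis fixes the difference at 20 points, the SD is fixed too and can be solved for. The answer is far wider than one expects of a 0–100 anxiety score.

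What is at stake is the meaning of the result, not its validity. If the SD is more usual, the trial has 80% power for a difference clearly smaller than 20 points. A statistically significant result could then come from an effect well short of the hypothesised one. A reader of the protocol could not tell which effect the trial was built to detect.

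**Working it through.** **Inputs.** From Sample size {14}: 75 per group, 15% dropout, 80% power, 5% type 1 error. From Hypothesis {6b}: a difference of 20 points. Two-sided testing is my assumption, taken from the planned 95% confidence intervals. The SD is not given, so I solve for it.

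**Step 1: evaluable per arm.** 75 × 0.85 = 63.75, about 64.

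**Step 2: detectable standardised difference.** Normal approximation: d = (1.960 + 0.842) × √(2/63.75) = 2.802 × 0.1771 = 0.496. The two-sample t-test gives d = 0.500.

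**Step 3: implied SD.** 20 / 0.500 = 40.0 (t), or 40.3 (normal).

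**Step 4: reproduce the plan's figure.** With SD 40 and a 20-point difference, the normal formula gives 63 per group. 63 / 0.85 = 74.1, rounded up to 75. The stated size is therefore recovered at SD 40, that is, at a standardised difference of 0.50.

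**Step 5: other conventions.**
- Alpha 0.025, for two time points: d = 0.55, SD about 36.
- Dropout ignored (75 per arm): d = 0.46, SD about 43.
- One-sided 5%: SD about 45.

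None brings the SD down to 33.3.

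**Step 6: how large is an SD of 40 on a 0–100 scale?**
- Maximum for any distribution: 50 (half the scores at each end).
- Maximum for a single-peaked distribution: 100/3 = 33.3.
- Uniform distribution: 100/√12 = 28.9.

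An SD of 40 needs scores heaped towards both ends. In the planned model the relevant quantity is the SD left after baseline adjustment. At a baseline correlation of 0.5 (assumed), a residual SD of 40 would need a raw SD of 40/√(1 − 0.25) = 46.2.

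**Step 7: what 64 per arm delivers.** SDs are assumed; two-sample t-test, two-sided 5%.

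| SD | Power for 20 points | Difference with 80% power | Smallest significant observed difference |
|---|---|---|---|
| 25 | 99.4% | 12.5 | 8.7 |
| 30 | 96.3% | 15.0 | 10.5 |
| 33.3 | 92% | 16.6 | 11.7 |
| 35 | 89% | 17.5 | 12.2 |
| 40 | 80% | 20.0 | 14.0 |

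The last column is 1.98 × SD × √(2/64).

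**Step 8: readings that might rescue the sentence.**
- *Change-score SD.* A raw SD of about 28 with near-zero correlation gives a change SD of √2 × 28 = 39.6. But Statistical plan {20a} analyses baseline-adjusted scores. With zero correlation the residual SD stays about 28, and power for 20 points is about 98%.
- *Relative 20%.* At an assumed mean of 50 to 70 this is 10 to 14 points, and the implied SD is an unremarkable 20 to 28. But then 20 points was not what was powered, and the hypothesis disagrees.
- *A generic standardised effect of 0.50.* Again, 20 points was not what was powered.

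**The case against.** The strongest reply is that nothing printed is contradicted. The stated numbers close exactly at a standardised difference of 0.50. An SD of 40 is below the mathematical maximum of 50. The calculation rests on an earlier study that cannot be consulted here, and an article that condenses a fuller protocol may leave the SD to that document. All of this stands. The absence of a printed SD is not the point, and a claim that the arithmetic is proven wrong would go too far.

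It is also fair that a 20% change on a 100-point scale most naturally means 20 points, so Sample size {14} and Hypothesis {6b} conflict only under the relative reading.

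A reader might argue further from the Discussion's statement, "Screening for moderate to severe anxiety ensures that the study population requires treatment", that enrolled patients must be too alike for an SD of 40. The documents do not support that step. Screening uses the APAIS, whereas the analysed outcome is VAS-A at T2 and T3, the latter after surgery. An APAIS threshold puts no bound on the spread of those scores.

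Two other points stand. In any trial with 80% power, an observed difference of about 70% of the target already reaches significance, so that alone is no defect here. The planned confidence intervals already let a reader judge 20 points directly.

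What the reply does not supply is a reading under which the sentence holds with a single-peaked VAS-A score and the planned analysis. The change-score, relative and generic readings each mean that 80% is not the power for 20 points.

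**Conclusion.** The point holds as an argument from implausibility. The stated 80% power for 20 points requires an SD of about 40 (36 with alpha 0.025, 43 with dropout ignored). That exceeds the 33.3 limit for a single-peaked score and is less plausible still as a residual SD after baseline adjustment. Unless VAS-A scores are strongly two-peaked, either the 80% or the 20 points is misstated. At the 33.3 limit, power for 20 points is 92% and the difference with 80% power is 16.6 points; at smaller SDs the gap widens.

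This rests on two-sided 5% testing, about 64 evaluable per arm and a simple comparison of means at one time point.

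Two stronger inferences should be avoided. The trial is not underpowered for 20 points: an SD below 40 gives more than 80% power. Nor can one say without condition that power exceeds 96%, or that an observed difference under 10 points would be significant. The first needs an SD of about 30 or less and the second an SD of about 28 or less, and the documents establish neither. The hypothesis also sets no rule that a significant p-value confirms 20 points; the risk is one of interpretation.

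**What to change.** Keep 150 participants and change the wording in three places.

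1. Sample size {14}: state that 64 evaluable per arm give 80% power, at two-sided 5%, for a standardised difference of 0.50. Give the corresponding point difference, and the power for 20 points, at the SD actually taken from the source study. If that SD cannot be recovered, give both over a range of SDs labelled as assumed, as in the table above.
2. Sample size {14} and Hypothesis {6b}: say that 20% means 20 absolute points on the VAS-A. If a relative change was intended, correct the hypothesis to match.
3. Hypothesis {6b} or Statistical plan {20a}: say that the 20-point hypothesis will be judged from the 95% confidence interval already planned, not from p < 0.05 alone.

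The cost is wording only, with no change to enrolment, data collection or the analysis model.

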### Statistical plan {20a}

Characteristics of groups will be summarised using counts and percentages for categorical variables and means and standard deviations for continuous variables. The primary outcome (anxiety at Time 2 and Time 3 in stacked format) will be compared between groups at each follow-up time point using a linear mixed-effects regression model, with fixed effects including treatment arm time (categorical), the interaction between treatment and time, anxiety time point (either Time 2 or Time 3), surgical type (stratification variable), and the baseline value of the outcome variable. Differences in mean VAS-A scores between groups at each time point will be presented together with 95% confidence intervals and *p*-values. Continuous secondary outcomes with repeated measurements will be compared using the same model. Hospital length of stay will be compared using the rank-sum test. Patient satisfaction will be compared using an independent sample *t*-test and descriptive statistics will be used to summarise the VRSQ.

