## Methods

### Study design and setting {8} {9}

A two-group parallel, single-centre, superiority, randomised controlled trial (RCT) with an allocation ratio of 1:1 will be conducted and reported in accordance with the CONSORT guidelines [27]. A total of 150 patients undergoing elective surgery will be randomised to the control (standard preoperative care) or intervention (standard preoperative care plus VR intervention) groups. The intervention will be delivered using the Oculus Quest 2 Virtual Reality Headset™ fitted with a smartphone (Fig. 1). This device has been chosen because it is the most advanced commercially available all-in-one VR device from Oculus, equipped with a highly immersive headset, two controllers, and integrated headphones. This study will be conducted in the surgical unit of a major Australian metropolitan hospital.

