### *Outcomes {12}*

#### Primary outcome

Perioperative anxiety will be assessed by the Research Assistant at three time points: on admission to the preoperative area (T1), immediately before surgery (T2), and 1 h on arrival to the post-anaesthesia care unit (T3). Participants will be asked to rate their level of anxiety using the visual analogue scale for anxiety (VAS-A). The VAS-A is valid, reliable, and frequently used to evaluate perioperative anxiety levels in surgical populations [35]. The VAS-A consists of a 100-mm horizontal line representing two behavioural extremes at either end of the continuum (i.e., ‘not at all anxious’ = 0, whereas ‘extremely anxious’ = 100). Scores on the VAS-A of 25 or higher reflect significant levels of anxiety [35].

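### The primary model gives baseline anxiety one slope for both T2 and T3; if the true slopes differ, a little precision is lost that a baseline-by-time term would recover almost free

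*Protocol article*

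**What the plan says.** The Statistical plan describes a linear mixed-effects model for VAS-A at T2 and T3. Its fixed effects are treatment arm, time, the treatment-by-time interaction, surgical type "and the baseline value of the outcome variable". Only one interaction is named. The group differences at each time, with their confidence intervals and p-values, are the primary result. Repeated continuous secondary outcomes use the same model.

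Under Primary outcome, anxiety is rated on admission to the preoperative area (T1), then "immediately before surgery (T2), and 1 h on arrival to the post-anaesthesia care unit (T3"). T1 is therefore the baseline, with one follow-up before surgery and one after it.

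Sample size {14} states that "a sample of 150 participants (75 per group) will provide 80% power" and allows for 15% dropout. It gives no SD and no correlation between time points, and does not mention baseline adjustment.

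**The concern.** The listed model lets the treatment effect change between T2 and T3 but holds the baseline effect constant. T1 and T2 are both pre-operative self-ratings on the same scale. T3 comes after the surgery that the patient was anxious about, and after an anaesthetic. A patient's T1 score could well say more about T2 than about T3.

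If so, a single slope settles between the two true slopes. It adjusts too little at one time and too much at the other, and leaves baseline variation in the residual that the trial could have removed. What is at stake is the width of the two primary confidence intervals. Heart rate, also measured at T1, T2 and T3, would share the loss. Salivary cortisol (T1 and T2) and pain (T1 and T3) have one follow-up each, so the point does not arise for them.

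**Working it through.** **The plan's own figure.** The sample size can only be back-solved. With two-sided 5% error (sidedness is not stated), 80% power and a 20-point difference, n per group = 2 × (1.96 + 0.84)² × SD² / 20². An SD of 40 gives 63 per group, and 63 / 0.85 = 74.1, rounded up to 75. So 150 fits an unstated SD of about 40 but cannot be verified. The relative widening below depends only on correlations and SD ratios, not on the absolute SD.

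**Formula.** Let b₂ and b₃ be the true slopes of T2 and T3 on T1, and S the 2×2 covariance of T2 and T3 given T1. With an unstructured covariance, the common slope tends to the generalised-least-squares average b = (1′S⁻¹β)/(1′S⁻¹1), where β = (b₂, b₃). The residual variance at time t rises from S_tt to S_tt + (b_t − b)² × Var(T1). The interval widens by the square root of that ratio.

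**Worked case (assumed).** Take r(T1,T2) = 0.7, r(T1,T3) = 0.3, r(T2,T3) = 0.4, and all SDs equal and scaled to 1.

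- S₂₂ = 1 − 0.49 = 0.51; S₃₃ = 1 − 0.09 = 0.91; S₂₃ = 0.4 − 0.21 = 0.19.
- The weights are proportional to 0.91 − 0.19 = 0.72 and 0.51 − 0.19 = 0.32, so b = (0.72 × 0.7 + 0.32 × 0.3) / 1.04 = 0.577.
- T2: (0.7 − 0.577)² / 0.51 = 3.0% more variance, or 1.5% more width.
- T3: (0.3 − 0.577)² / 0.91 = 8.4% more variance, or 4.1% more width.

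**Range.** Extra interval width from the common slope, equal SDs, all correlations assumed:

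| r(T1,T2) / r(T1,T3) / r(T2,T3) | Unstructured, T2 | Unstructured, T3 | Random intercept, both times | Simulated SE ratio |
|---|---|---|---|---|
| 0.5 / 0.5 / 0.5 | 0% | 0% | 0% | 0.998 |
| 0.6 / 0.4 / 0.5 | 0.5% | 0.9% | 0.7% | 1.005 |
| 0.7 / 0.3 / 0.4 | 1.5% | 4.1% | 2.8% | 1.026 |
| 0.7 / 0.3 / 0.6 | 0.6% | 5.6% | 2.8% | not run |
| 0.8 / 0.2 / 0.3 | 2.2% | 11.1% | 6.6% | 1.063 |

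The last column is the model-based standard error with one slope divided by that with separate slopes. It comes from a random-intercept REML simulation with 64 per group, SD 25 and 200 replicates.

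If the SD at T3 is 18 against 25 at T1 and T2, the widening at T2 and T3 is 3.1% and 1.4% for correlations 0.6/0.4/0.5, 6.2% and 5.4% for 0.7/0.3/0.4, and 8.9% and 14.7% for the extreme 0.8/0.2/0.3.

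**In points.** In the 0.7/0.3/0.4 simulation the standard errors were 3.83 and 3.73, so the 95% half-widths were 1.96 × 3.83 = 7.5 and 1.96 × 3.73 = 7.3. The difference is 0.2 point against a 20-point target. Scaled to an SD of 40 (× 40/25 = 1.6), it is about 0.3 point.

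**In participants.** With about 128 evaluable, an extra variance f is worth 128 × f/(1 + f). For 3.0% that is about 4 participants, and for 8.4% about 10.

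**Bias.** The simulations had no true treatment effect. In the 0.7/0.3/0.4 case the mean estimates were −0.23 (T2) and −0.04 (T3) with one slope, and −0.24 and −0.03 with two. The common slope introduced no bias.

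**The case against.** The strongest objection is that nothing in the text is wrong. The list of fixed effects is introduced as what the model includes, in a condensed article, so a baseline-by-time term is unlisted rather than ruled out. That stands as a reason not to call this an error. But the terms are itemised and one interaction is named, so an analyst who follows the text would fit a single slope.

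The second objection is that unequal slopes are assumed. This also stands. A reader might infer from the timing that T1 does predict T2 and T3 differently, and that both intervals are therefore widened. The documents show neither. The interval between T1 and T2 is not stated. The VR session is meant to change anxiety before T2 and could weaken the T1–T2 link. Entry requires an APAIS anxiety score of 11 or more, which probably narrows the baseline spread and so the penalty. Even with clearly unequal slopes, the loss at T2 can be as small as 0.6%.

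Third, a reader might infer that the stated power is eroded. It is not shown to be, since the sample-size statement claims no gain from baseline adjustment. With slopes 0.7/0.3, equal SDs and a common slope of 0.5, residual variance relative to no adjustment is 0.51 + 0.04 = 0.55 at T2 and 0.91 + 0.04 = 0.95 at T3. The listed model still beats an unadjusted comparison.

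Finally, a reader might suspect a distorted type I error if T2 and T3 have unequal variances. That is a separate matter. It needs a forced common residual variance, and the protocol states no covariance structure.

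**Conclusion.** The point holds as a conditional, minor one about efficiency. As listed, the primary model has a single baseline slope for T2 and T3. If the true slopes differ, which is plausible but undocumented, the time-specific differences are estimated a little less precisely than they could be. For slopes of 0.6/0.4 to 0.7/0.3 with equal SDs and a T2–T3 correlation of 0.3 to 0.5, intervals are about 0.5% to 4% wider. A T2–T3 correlation of 0.6 takes T3 to 5.6%. Double-digit widening needs the extreme slopes, with or without a smaller SD at T3, and equal slopes give no loss. Every correlation and SD used is an assumption. The treatment estimates remain unbiased, and the validity of the comparison is not in question.

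**What to change.** Add a baseline-by-time interaction to the fixed effects of the primary model, so that T2 and T3 each have their own baseline slope, and do the same in the heart-rate model. Record it before the statistician sees allocation. An unstructured 2×2 residual covariance for the two follow-up times is an optional addition.

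The cost is one sentence and one parameter per model, with no further data or participants. If the slopes turn out equal, the price is negligible: the simulated common-slope standard error was only 0.2% smaller (ratio 0.998).

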
**Fig. 3 Fig3:**
[figure not shown]
Study flow diagram

**Table 1 Tab1:** SPIRIT flow diagram

Study period							
	Pre-admission	Preoperative phase			Postoperative phase		Discharge
Timepoint^a^	−t_1_	t_0_	t_1_	t_2_	t_3_	t_4_	t_5_
Enrolment:							
Eligibility	X						
Informed consent	X						
Screen Anxiety level		X					
Allocation		X					
Interventions:							
VR exposure				X			
Assessments:							
**Primary outcome:**			X	X	X		
Perioperative anxiety							
**Secondary outcomes**:			X	X	X		
Stress level							
Pain			X		X		
Patient satisfaction						X	
Length of hospital stay							X
VR adverse effect				X			

^a^−t_1_, pre-admission; t_0_, on admission to hospital; t_1_, on admission to preoperative area; t_2_, immediately before surgery (holding area); t_3_, 1 h post-surgery; t_4_, after 24 h post-surgery and before discharge; t_5_, post-discharge

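### Anxiety at T2 and T3 is jointly primary under one stated 5% error rate and 80% power, with no rule for which result decides the trial

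*Protocol article*

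**What the plan says.** The Statistical plan section defines the primary outcome as anxiety at Time 2 and Time 3, stacked in one linear mixed model that includes a treatment-by-time interaction and the baseline score. The outcome "will be compared between groups at each follow-up time point", and "Differences in mean VAS-A scores between groups at each time point will be presented together with 95% confidence intervals" and p-values.

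The Primary outcome section lists T1, T2 and T3 without ranking them. T1 serves as baseline, so two follow-up comparisons remain. The Hypothesis section gives one expected effect, 20 points on the VAS-A, for perioperative anxiety as a whole and ties it to no time point.

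The Sample size section claims "80% power to detect a 20% change on the 100-point VAS-A between groups" with 150 participants, a type 1 error rate of 5% and 15% dropout. It does not say which time point the power refers to.

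No section gives a deciding time point, a joint test, a rule on whether one or both results must be significant, or a testing order.

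**The concern.** With the interaction in the model, the analysis yields two separate treatment effects, each with its own p-value, and both carry the label of primary outcome. They answer different questions. T2 is taken in the holding area, where the VR session is given. T3 comes after anaesthesia and surgery. An effect that is present at T2 and gone by T3 is quite possible, so a mixed result is a realistic outcome.

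The protocol gives no reading of a mixed result. The claim that VR reduces perioperative anxiety could then rest on whichever time point turned out significant, chosen after the data are seen. In that case the 5% in the Sample size section would not describe the chance of a false claim. If instead both results were needed, the 80% would not describe the chance of success.

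**Working it through.** **Inputs**

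- Type 1 error 5%, power 80%, difference 20 points, 75 per group, dropout 15%: Sample size section.
- Number of primary comparisons, 2 (T2 and T3): Statistical plan section.
- Two-sided testing at 5% each: not stated, inferred from the 95% confidence intervals and the 5% error rate.
- SD of the VAS-A: not stated.
- Correlation ρ between the T2 and T3 test statistics: not stated, assumed 0 to 0.9.

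**Step 1: the plan's own figure.** For one two-sided 5% test with 80% power, n per arm = 2 × (1.960 + 0.842)² × (SD/20)². No SD is given, so 150 cannot be checked independently. With SD = 40, n = 2 × 7.85 × 4 = 62.8, rounded up to 63. Then 63/0.85 = 74.1, rounded up to 75 per arm, or 150 in total. The stated size therefore fits one 5% comparison if the SD is about 40.

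**Step 2: either time point counts as success.** Family-wise error = 1 − P(|Z₁| < 1.96 and |Z₂| < 1.96), with (Z₁, Z₂) bivariate normal with correlation ρ. At ρ = 0 this is 1 − 0.95² = 0.0975.

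| Assumed ρ | Family-wise error |
|---|---|
| 0 | 9.75% |
| 0.3 | 9.51% |
| 0.5 | 9.07% |
| 0.7 | 8.35% |
| 0.9 | 7.04% |

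The same patients supply both scores, so ρ = 0 is a bound and not an expectation. Relative to 5%, the range is 7.04/5 = 1.4 times to 9.75/5 = 1.95 times.

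**Step 3: both time points must be significant.** The chance that both tests reject cannot exceed the chance that one does, so the error is at most 5%. Taking 80% power at each time, joint power is 0.80 × 0.80 = 64% if the tests are independent. It rises with correlation and reaches 80% only when they are perfectly correlated.

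**Step 4: one pre-specified sequence.** Suppose T2 is tested at 5%, and T3 is tested at 5% only if T2 is significant. If there is no T2 effect, any false claim needs a false rejection at T2, which has probability at most 5%. If there is a T2 effect, the only possible false claim is at T3, again at most 5%. Family-wise error is 5% at most, and the T2 test keeps its full 5%.

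**The case against.** The strongest reply is that the documents never say success at either time is enough. The Statistical plan says that differences will be presented, which is a statement about reporting and not a rule for claiming success. A reader might infer that the trial's type 1 error nearly doubles as the plan stands. The documents do not support that: the inflation needs an either-counts rule that appears nowhere, and near-doubling is the upper end of an assumed correlation range. This part of the objection stands, and it is why the result is given conditionally.

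A reader might also take it as established that 150 was computed for a single 5% test. With no SD stated, the number alone cannot show this. With 75 × 0.85 = 63.75 completers per arm, a 2.5% test with 80% power fits an SD of 20/[(2.241 + 0.842) × √(2/63.75)], about 36.6, just as well. What supports the single-comparison reading is the wording: one difference, one error rate, no split mentioned.

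It can further be said that alpha sharing and testing order are often left to the analysis plan, and that this is a condensed article. That is fair for the mechanics. It does not cover the definition of the primary outcome, which the protocol itself fixes as two time points beside one error rate and one power figure. Nor does the single mixed model settle the matter: it shares information across times but does not control error over two separately reported contrasts.

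Finally, making T2 the sole primary time point would narrow an aim stated in terms of perioperative anxiety. That objection also stands, so T2-first is one valid option among several.

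**Conclusion.** The gap is real, and its consequence depends on the rule that is missing. The stated 5% and 80% are both correct only for one primary comparison, and the protocol defines two without joining them. If either counts, the family-wise error is about 7.0% to 9.8% for assumed correlations of 0.9 to 0, and about 8.4% to 9.5% for 0.7 to 0.3. If both are required, the error is within 5% but power is below 80%, and as low as 64% under independence. These figures assume two-sided 5% tests and, for power, 80% at each time point. The correlation and the SD are not in the documents.

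The T3 definition also differs between sections. The Primary and Secondary outcomes sections time it from arrival in the post-anaesthesia care unit, while the Table 1 footnote reads "t_3_, 1 h post-surgery". A reader might count this as further evidence here, but it has no bearing on multiplicity and should be reconciled as a separate matter.

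**What to change.** Before unblinding, pre-specify one primary test at two-sided 5% from the mixed model already planned, and record it as a dated amendment in the protocol and the registry. Two ways to do this:

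- **Fixed sequence.** For example, test the T2 difference first and claim T3 only if T2 is significant. This needs no extra patients and costs no alpha at T2. The downside is that T3 cannot be claimed alone.
- **One effect over both times.** Use a single joint test, or the treatment effect averaged over T2 and T3, and report the time-specific differences as supportive. This keeps the perioperative aim. The downside of the average is dilution if the effect fades: 20 points at T2 and 0 at T3 average to 10.

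A Bonferroni split (2.5% at each time) is also valid but costs more. If the SD is about 40, power per time point at 64 completers per arm falls from about 81% to about 72%. Restoring 80% would need 77 completers per arm, and 77/0.85 = 90.6, so 91 per arm or 182 in total. With an SD of 30, power at 2.5% would still be about 94%.

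Under any option, state in the Sample size section which comparison the 80% power refers to. The wording takes a few sentences, but recruitment is already under way according to the Trial status section. The change therefore alters the primary outcome during the trial, and the amendment should show that it was made without sight of results by group.
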